### Randomization

Randomization sequence will be generated using an online randomization website (www.randomisation.com). Block randomization will be done using blocks of 12 to generate the randomization schedule for 240 patients. The patients will be allocated to treatments based on the randomization sequence generated. One week’s supply of the assigned investigational products will be handed over to the patients according to the randomized allocation. Each group will be enrolled with an allocation ratio 1:1:1.The allocation for each randomization number will be put in to individually seal opaque envelops. The envelopes and allocation sequence will be kept under lock and key by one investigator not involved in recruiting patients. The patients meeting inclusion exclusion criteria and recruited into the study will be assigned a randomization number sequentially, according to the date and time of recruitment. The allocated treatments indicated in the sealed envelope for each randomization number will be supplied to each patient. The study design flow chart is shown in Fig. 1.

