## Methods

### Study design

This is a three-arm, open-label non-inferiority randomized controlled clinical trial that will be conducted at the National Ayurveda Teaching Hospital in Colombo, Sri Lanka. TMD12, used in traditional Ayurveda, and its freeze-dried formulation will be the test products. The efficacy and safety of the two Ayurvedic dosage forms will be tested against the antihistamine loratadine. Patients with symptoms of AR will be allocated randomly into the three arms after a 1-week run-in period and the medications given orally for 28 days. This study protocol was developed as required by the Standard Protocol Items: Recommendations for Interventional Trials (SPIRIT) (Additional file 1).

Ethics approval has been obtained from Ethics Review Committee, Institute of Indigenous Medicine (ERCIIM), University of Colombo, Sri Lanka (ERC 18/76) and the Ethics Committee of the Faculty of Medicine, University of Colombo, Sri Lanka (EC-18-090). The trial was registered in the ISRCTN registry (Trial number ISRCTN18149439) (Additional file 2).

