### Data handling, record keeping, and dissemination

An individual file for each participant will be used to archive a hard copy of the case record forms including informed consent, results of the hematological and biochemical investigations, results of the physical examinations, and completed questionnaires. Data will be entered by a minimum number of dedicated staff and saved in a dedicated computer with password protection. These data will be retained with the researchers and will not be handed over to any other party under any circumstances. The study participant’s information will be securely stored at each clinic visit during the study. At the end of the study, all records will continue to be kept in a secure location for a 2-year period.

Study participants’ data will be stored at the department of Dravyaguna Vignana, IIM, which will be used for statistical analysis and scientific reporting. Each participant’s contact or identifying information will be separately stored. Individual participants and their research data will be identified by a unique study identification number. At the end of the study, all study databases will be de-identified and archived. A data safety monitoring board has been appointed according to the guidelines of Ethics Review Committee of Faculty of Medicine for safety monitoring. The board consists of three independent expert members. Further, we have not planned the auditing of this clinical trial, because it is a single-center trial involving only 210 patients. The results of the study will be used for scientific reporting in conferences and will be published in peer-reviewed journals. Further results of the study and the grouping information of the participants will be provided to the individual after completion of the trial.

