## Trial status

This protocol is version 1. The recruitment is currently in progress and it is expected that the recruitment will be completed by the end of May 2021.

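### A single disclosed block length of 12 in an open-label, single-centre trial could let a recruiter predict up to about 11% of allocations with certainty; varying the length is a cheap improvement

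*Protocol article*

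**What the plan says.** All references are to the protocol article.

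- **Block length and list.** Randomization: "Block randomization will be done using blocks of 12". The list produced this way covers 240 patients. On the ratio, the same section says: "Each group will be enrolled with an allocation ratio 1:1:1". Numbers are given out in order of the date and time of recruitment, and no strata are mentioned.
- **Safeguards.** The same section has each allocation sealed in its own opaque envelope. On custody it says: "The envelopes and allocation sequence will be kept under lock and key by one investigator not involved in recruiting patients".
- **Blinding.** Study design: "This is a three-arm, open-label non-inferiority randomized controlled clinical trial". The same section places allocation after a 1-week run-in.
- **Size and sites.** Data handling, record keeping, and dissemination gives the reason for not planning an audit: "because it is a single-center trial involving only 210 patients".
- **Timing.** Trial status: "The recruitment is currently in progress", with completion expected by the end of May 2021.
- **Who does what.** Under Recruitment, the investigators take consent and complete the baseline forms. Under Safety assessment, the investigators record adverse events at each weekly clinic visit.

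**The concern.** With one known block length, anyone who sees the treatments given so far can count down the places left in the block. Once two arms are full, the rest of the block is known. The three products are plainly different (a herb pack to boil, a sachet of powder, a tablet) and are dispensed weekly in the trial clinic, so an investigator could keep such a tally in the course of ordinary work. The envelopes and the locked list protect against reading ahead, not against deduction from open past allocations.

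Foreknowledge matters because entry leaves room for judgement. The exclusion criteria end with a general power for investigators to exclude patients they think unsuitable, and entry also needs a Total Nasal Symptom Score (TNSS) above 6 on forms that investigators complete. A recruiter who knows the next arm could delay or turn away a patient. The primary outcome is a subjective symptom score, so arms that differ in prognosis or expectation could differ on it for reasons other than treatment.

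**Working it through.** The article gives no predictability figure to reproduce. Its own numbers fix the structure: 240/12 = 20 blocks on the schedule; 12/3 = 4 places per arm per block; 210/12 = 17.5, so the planned 210 patients use 17 full blocks and the first 6 places of an eighteenth.

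**1. Certain allocations, full tally assumed.** An allocation is certain when only one arm still has places in the block. The number of such places equals the length R of the run of identical allocations at the end of the block.

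- P(R ≥ 1) = 1
- P(R ≥ 2) = 3/11 = 0.2727
- P(R ≥ 3) = (3/11)(2/10) = 0.0545
- P(R = 4) = (3/11)(2/10)(1/9) = 0.0061
- E(R) = 1 + 0.2727 + 0.0545 + 0.0061 = 4/3 per block, and (4/3)/12 = 11.1%

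Over 240 patients: 20 × 4/3 = 26.7 (11.1%). Over 210: 17 × 4/3 = 22.7, or 22.7/210 = 10.8%. The last 6 patients add none, because two arms cannot be full before 8 places are used. A simulation of 200,000 blocks gave 1.334 per block.

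**2. At least one arm ruled out.** Exact recursion gives 52/15 = 3.47 places per block (28.9%). Over 210 patients: 17 × 3.467 + 0.036 for the part-block = 58.97, or 28.1%.

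**3. Best guess.** A recruiter who always names the most likely arm is right for 51.2% of places in full blocks (33.3% by chance), and for about 51% over 210 patients.

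**4. Effect of the run-in.** Suppose numbers are assigned at recruitment and opened a week later, so that L predecessors in the list are still unrevealed when the recruiter decides. Certainty then needs a terminal run longer than L, and the expected count per block is the sum of P(R ≥ j) for j > L.

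| Unrevealed predecessors | Certain places per block | Share of a block | Number in 210 (17 blocks) |
|---|---|---|---|
| 0 | 1.3333 | 11.1% | 22.7 |
| 1 | 0.3333 | 2.8% | 5.7 |
| 2 | 0.0606 | 0.5% | 1.0 |

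The recruitment rate is not given, so L is an assumption.

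**5. Varied lengths.** Simulated sequences of 210 patients, for a recruiter who knows the set of lengths and all past allocations but not the order of the lengths:

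| Block lengths | Certain | At least one arm ruled out | Best guess correct |
|---|---|---|---|
| 12 only | 10.8% | 28% | 51% |
| 9, 12, 15 | about 1.9% | about 5.5% | 51% |
| 12, 15, 18 | about 1.6% | about 4.7% | 49% |
| 12, 15, 18, 21, 24 | about 0.6% | about 1.9% | 48% |

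In patients, certain allocations fall from about 23 to about 4 (0.019 × 210) or about 1 (0.006 × 210).

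**6. Is 12 too short?** Certain shares for a single length are 20% at 6, 14.3% at 9, 11.1% at 12 and 9.1% at 15. Twelve is the least predictable of the lengths up to 12. The weakness is that there is one length and that it is disclosed, not that the block is short.

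**The case against.** **The run-in may already do most of the work.** Study design puts allocation after a 1-week run-in, while Randomization orders numbers by recruitment. If eligibility is settled at recruitment and the envelope is opened a week later, two unrevealed predecessors would bring certainty to 0.5%, as low as the best of the varied schemes above. This stands as a limit on the size. It does not dispose of the point: the article does not say when numbers are assigned relative to the run-in. If numbers are assigned and opened together afterwards, and patients can still be held back then, the full figure applies.

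**Varying the length hardly changes the best-guess rate.** This is true (51% to about 48 to 51%), and steering needs only a probable guess. But acting dependably on a particular patient is easiest when the arm is known or one arm is excluded, and both of those fall about five-fold or more.

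**A full tally is inferred.** A reader might conclude that recruiters learn every past allocation and that concealment is defeated. The article supports less. Investigators see treated patients weekly and unblinded, so a tally is feasible, but no section says that anyone holds a complete ordered one or has used it.

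**The analysis offers some protection.** A reader might also infer that any resulting bias is beyond repair. That goes too far: the analysis section plans ANCOVA for possible confounders, which can address measured baseline differences such as baseline TNSS. It cannot be relied on for unmeasured ones. No bias in the outcome has been quantified here.

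**The change may come late.** The published length cannot be withdrawn, and the number of unused randomisation numbers is unknown.

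**Conclusion.** The point holds as a cheap improvement to a design choice, not as an error or contradiction in the plan. One disclosed length of 12 on a single sequential list, in an open-label single-centre trial, makes up to about 11% of allocations (about 23 of 210) predictable with certainty and lets at least one arm be ruled out for about 28%. Both are averages and upper bounds. They assume a recruiter who knows the length, has a complete tally of the current block, and decides on entry with no earlier allocation unrevealed. With one or two unrevealed, certainty is about 2.8% or 0.5%. The stated safeguards do not close this route, so concealment can be weakened; the documents do not show that it has been.

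**What to change.** - **New schedule for unused numbers only.** The non-recruiting investigator who holds the list generates it with block lengths drawn at random in multiples of 3, for example from 12, 15, 18, 21 and 24. Allocations already made stay as they are. Starting at the end of the block in use preserves the balance reached so far.
- **Do not disclose the lengths.** Keep the new lengths, and preferably their range, from recruiting staff and out of protocol text until enrolment closes.
- **State the timing.** Say whether a randomisation number is assigned at recruitment or after the run-in, and whether a patient can still be excluded once the number is assigned. This settles which of the figures above applies.
- **Notify** both ethics committees and the registry, as Ethical considerations already provides for protocol modifications.
- **If enrolment has closed,** report the single published length as a limitation.

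The cost is one new list, new envelopes and the notices. The arms may end a few patients apart: stopping inside a block of 24 can leave at most 24/3 = 8 between two arms. The present scheme can already leave up to 4, since 210 is not a multiple of 12. Certain allocations fall to about 0.5 to 2%; general predictability falls only slightly.

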## Background

Allergic rhinitis is an IgE-mediated immunological response of nasal mucosa to air-borne allergens and is characterized by nasal congestion, watery nasal discharge, itching of the nose, and sneezing. It is commonly defined as seasonal or perennial, depending upon whether symptoms are manifested at defined yearly intervals or throughout the year, respectively [1]. Allergic rhinitis is not life threatening, but for the patient it is an annoying and disturbing disease due to its chronicity and aggravation during exposure to allergic agents. Furthermore, allergic rhinitis is a considerable cause of widespread morbidity, medical treatment costs, reduced work productivity, and lost school days [2]. The symptoms of allergic rhinitis may significantly affect a patient’s quality of life and can be associated with conditions such as fatigue, headache, cognitive impairment, and sleep disturbances [3]. Appropriate management of allergic rhinitis is an important component in effective management of coexisting respiratory conditions such as asthma, sinusitis, and sleep apnea [4].

The World Allergy Organization (WAO) reports the prevalence of rhinitis symptoms in the International Study on Asthma and Allergies in Childhood (ISAAC) to vary between 0.8% and 14.9% in 6 to 7-year-olds and between 1.4% and 39.7% in 13 to 14-year-olds [5]. The reported prevalence in adults ranges from 8.7 to 24.1% in China and 11.4 to 22.7% in Turkey [6]. Also, in the USA, an estimated 20% of cases are seasonal allergic rhinitis and 40% of cases are perennial rhinitis [7].

In Sri Lanka, many people suffer from this condition. A survey of 6000 patients attending the OPD at the Teaching Hospital, Ragama, Sri Lanka, identified allergic manifestations in 8.8% of patients, and 22% of them had rhinitis [8]. Another survey conducted in Sri Lanka among schoolchildren in grade 5 from Western province, Sri Lanka, found symptoms of allergic rhinitis in 21.4% children with a statistically significant higher prevalence in boys [9]. The reason for this observation was not discussed in the paper.

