### Sample size

Sample size was calculated based on the primary outcome measurement of TNSS and as for a non-inferiority clinical trial. This study is designed to evaluate the comparative clinical efficacy and safety of two Ayurvedic dosage forms with the antihistamine loratadine, assuming non-inferiority-between the three interventions. Sample size was calculated as specified by Hampel et al. [11]. According to a previous study done among patients with allergic rhinitis using loratadine, clinically significant standardized effect sizes of TNSS are reported in the range of 0.57 to 0.67 [11]. Therefore, a standardized effect size of 0.5 was considered as the non-inferiority margin using the effect reported by Hampel and team.

Sample size was calculated for a significance level (**α**) of 5% and power of 80%. The sample size calculated using these values is 64 per group. With an expected dropout rate of 10%, minimum sample size was calculated as 70 for one arm.

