## Method of data analysis

For primary and secondary outcome measures, the mean values at baseline and at the end of the study and the mean differences will be compared between the three arms using ANOVA (analysis of variance) or the non-parametric Kruskal–Wallis test, depending on the normality of the data. Within each treatment arm, the difference in primary and secondary outcome measures before and after the intervention period will be compared using paired-sample *t* test or non-parametric Wilcoxon signed-rank test, depending on the normality of the data. 95% confidence intervals will be calculated for all outcome measures that are normally distributed. Categorical variables will be compared between groups using the Chi-square test. Possible confounders will be adjusted using ANCOVA. Following adjustment for confounding using ANCOVA, adjusted mean values with confidence intervals will be calculated and reported. Statistical analysis will be performed using the SPSS Statistical Package program (ver. 18.0), and the level of significance will be established at α = 0.05. Missing data at outcome assessment will be replaced with the available latest values of the outcome measure. Intention-to-treat analysis will be performed for all efficacy outcomes and safety outcomes. In addition, per-protocol analysis will be performed for the efficacy outcomes by including only the patients completing the follow-up.

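### Arms are balanced within consecutive blocks of 12, but the named between-arm analyses contain no block or calendar-period term; adding one is a nearly free gain in precision (low severity)

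*Protocol article*

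**What the plan says.** **Allocation (Randomization).** The schedule is described as "Block randomization will be done using blocks of 12 to generate the randomization schedule for 240 patients". The ratio is equal: "Each group will be enrolled with an allocation ratio 1:1:1". Each patient "will be assigned a randomization number sequentially, according to the date and time of recruitment". Blocks therefore fill in calendar order, and each full block holds four patients per arm.

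**Analysis (Method of data analysis).** For primary and secondary outcomes, "the mean differences will be compared between the three arms using ANOVA (analysis of variance"), with Kruskal–Wallis as the fallback if normality fails. The same section plans ANCOVA for possible confounding, with adjusted means and confidence intervals. It does not list the covariates, and it mentions neither block nor period.

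**Why time may matter.** The Background classifies allergic rhinitis as seasonal or perennial, "depending upon whether symptoms are manifested at defined yearly intervals or throughout the year". The Inclusion and exclusion criteria exclude neither type. Under Trial status, "it is expected that the recruitment will be completed by the end of May 2021". No start date is given; the registration date is May 2019.

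**Margin (Sample size).** "a standardized effect size of 0.5 was considered as the non-inferiority margin".

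**The concern.** Blocking in calendar order removes differences between enrolment periods from the comparison of arms. A one-way ANOVA leaves those same differences in the residual variance. If symptom levels vary from block to block, the estimated standard error then exceeds the true standard error of the arm difference, and the interval is wider than the design requires.

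The ANCOVA sentence does not clearly close this gap. It is aimed at confounders, and a factor balanced across arms by design is not one, so that rule gives no reason to include block. Kruskal–Wallis cannot include it at all.

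At stake is precision. In a non-inferiority comparison, a needlessly wide interval makes it harder to show that a herbal arm is within 0.5 SD of loratadine. It does not make a false claim of non-inferiority more likely.

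**Working it through.** **Inputs from the protocol article.** Margin 0.5 SD, alpha 5%, power 80%, 64 per group, 10% dropout, 70 per arm (Sample size); blocks of 12, ratio 1:1:1 (Randomization); 210 patients in total (Data handling, record keeping, and dissemination).

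**Assumptions.** The true difference is 0. A share ρ of the TNSS variance lies between blocks. The documents do not give ρ, so it is varied from 0 to 0.20.

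**1. The plan's own figure.** n = 2(z₀.₉₇₅ + z₀.₈₀)² / 0.5² = 2(1.960 + 0.842)² / 0.25 = 62.8, so 63 per group; the t-based version gives 64 (power 0.801). The stated 64 reproduces at one-sided 2.5%. One-sided 5% would give 50 (51 t-based).

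**2. Interval half-width with full blocks.** 64 per arm is 192 patients, or 16 blocks.

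- Unadjusted: t(189 df) × √(2/64) = 1.973 × 0.1768 = 0.349 SD, whatever ρ is.
- Block-adjusted: t(174 df) × √(2(1 − ρ)/64), with 174 = 189 − 15.

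| ρ (assumed) | Unadjusted | Block-adjusted | Unadjusted wider by |
|---|---|---|---|
| 0 | 0.349 | 0.349 | −0.06% (no gain) |
| 0.05 | 0.349 | 0.340 | 2.5% |
| 0.10 | 0.349 | 0.331 | 5.4% |
| 0.20 | 0.349 | 0.312 | 11.7% |

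At 70 per arm the ratios are the same, for example 0.333 against 0.316 at ρ = 0.10.

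**3. Coverage, type I error and power.** 4,000 simulated trials per setting, 192 patients, 95% interval, non-inferiority declared if the upper limit is below 0.5 SD. Ranges cover two forms of drift: random block effects and a smooth seasonal wave.

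| ρ | Coverage, unadjusted | One-sided type I error, unadjusted | Power, unadjusted | Power, block-adjusted |
|---|---|---|---|---|
| 0 | 0.951–0.952 | 0.022–0.025 | 0.79–0.80 | 0.79–0.80 |
| 0.05 | 0.957–0.960 | 0.021–0.023 | 0.81–0.82 | 0.83 |
| 0.10 | 0.959–0.960 | 0.021–0.022 | 0.81–0.82 | 0.84 |
| 0.20 | 0.969–0.972 | 0.014 | 0.83 | 0.88–0.89 |

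Block-adjusted coverage stayed at about 0.95 throughout. The simulation error of a power figure near 0.80 is √(0.8 × 0.2/4000) = 0.006.

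**4. With dropout.** 210 patients make 210/12 = 17.5 blocks, and 10% dropout leaves 70 × 0.9 = 63 per arm, so blocks are no longer exactly balanced. In a simulation of that case, the block-adjusted interval was 0.7% wider than the unadjusted one at ρ = 0, and about 2%, 4% and 9% narrower at ρ = 0.05, 0.10 and 0.20. Turned round, the unadjusted interval is 1/0.98, 1/0.96 and 1/0.91 times as wide, that is about 2%, 4% and 10% wider. Unadjusted coverage was about 95.5% to 96.5%, and power stayed near 80% or above. The intention-to-treat analysis carries last values forward, so it lies nearer step 2; the per-protocol analysis lies nearer step 4.

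**The case against.** The strongest reply is that ANCOVA is already planned, and that its covariate list belongs in a statistical analysis plan that is not shown. This stands in part: a missing list is not an error, and it would be wrong to infer that the analysis ignores time altogether. What remains is narrower. The tests that the article does name have no block term, and its stated reason for adjusting, confounding, does not point to a factor that the design has balanced.

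A second reply is that drift is unproven. This also stands. A reader might infer that the protocol calls the disease seasonal, but it says seasonal or perennial, reports no time trend in TNSS and gives no recruitment start date. Entry requires a TNSS above 6 on a 0–12 scale, which limits baseline drift, and comparing changes from baseline may remove part of any seasonal level. Drift at day 28 and at the follow-up visits one and two months later remains possible, but its size is unknown.

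A third reply is that no section says a confidence interval must lie within the margin; the 0.5 SD appears only under Sample size. That is literally so. Interval width still matters because the trial is designed for non-inferiority, but the point should not be presented as a breach of a stated decision rule.

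Finally, a reader might infer that the trial is underpowered or its inference invalid. The figures do not support that: with full blocks, unadjusted power is at or close to 80% at every setting and type I error does not exceed 2.5% beyond simulation error.

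**Conclusion.** The point holds as a low-severity improvement. The design matches the arms on enrolment period, and the named between-arm methods do not use that matching. If 5% to 20% of TNSS variance lies between blocks, the unadjusted interval is about 2% to 10% wider than it need be once dropout is allowed for (2.5% to 11.7% with full blocks). With no between-block variance, nothing is gained and adjustment costs under 1% in width. The size rests entirely on the assumed share and on a true difference of zero. The consequence is conservative inference and unused precision; neither type I error nor the planned power is compromised.

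**What to change.** In Method of data analysis, state that each herbal-minus-loratadine TNSS difference and its 95% confidence interval come from a linear model (the planned ANCOVA can serve) that includes randomisation block as a random effect, or calendar quarter of allocation as a fixed factor. Have this model supply the estimate and interval even if Kruskal–Wallis is also reported, since that test cannot carry the term. Name the factor before outcome data are analysed; the trial is open-label and already recruiting.

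The cost is one sentence. Block follows from the sequential randomisation number, so the only requirement is that number or the allocation date in the analysis data set. As a fixed effect, block uses 15 to 17 degrees of freedom (16 or 18 blocks, less one) out of about 190; a random effect or quarter would normally use fewer. Seasonal or perennial type should not be made a required covariate on the strength of this article, because it mentions only a complete history and does not say that the type is recorded.
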